#### Secondary outcomes

2.7.2

(1) Serum levels of AMH, FSH, LH: At baseline (week 0), after the 16-week intervention (week 16) and at the end of the follow-up period (week 32), venous blood samples will be collected during the early follicular phase (days 2–4 of the menstrual cycle) to measure AMH, FSH, and LH levels (32, 33).

(2) Scale Assessments: The following validated scales will be used to assess outcomes: Modified Kupperman Index (mKMI) (34): To evaluate the severity of menopausal symptoms. Hamilton Anxiety Scale (HAMA) (35) and Hamilton Depression Scale (HAMD) (36): To assess the effects of the intervention on anxiety and depressive symptoms. Menopause-Specific Quality of Life Questionnaire (MENQOL) (37): To assess health-related quality of life during the perimenopausal period. Assessments will be conducted at week 0, week 16, and week 32.

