#### Rs-fMRI

2.7.4

Resting-state functional magnetic resonance imaging (rs-fMRI) will be conducted at Hubei Provincial Hospital of Traditional Chinese Medicine. Each participant will undergo two MRI scans, at baseline (week 0) and after the 16-week intervention (week 16). For each participant, longitudinal MRI scans will be scheduled at a similar time of day whenever possible to minimize circadian-related variability in resting-state neural activity. Relevant pre-scan lifestyle factors, including sleep status, caffeine and alcohol intake, smoking status, and vigorous physical activity, will be recorded and considered when interpreting rs-fMRI findings. Before scanning, participants will be instructed to remove all metallic objects and wear noise-reducing earplugs. During scanning, participants will lie in a supine position, remain still, and keep their eyes closed while staying awake and relaxed. Foam cushions will be used to fix the head in place to minimize motion artifacts. This study will collect multimodal neuroimaging data to investigate the potential mechanisms by which the intervention modulates brain function and structure.

All imaging will be performed on a Siemens MAGNETOM Skyra 3.0 T MRI scanner using a 32-channel head coil. The imaging protocol includes a high-resolution T1-weighted structural sequence, rs-fMRI and diffusion weighted images (DWI) sequence. To exclude intracranial structural abnormalities that may interfere with the results, anatomical evaluation will be performed concurrently.

Scanning Parameters: High-resolution T1-weighted structural imaging (T1WI): Acquisition time = 280 s matrix = 256 × 256 × 176 slices, repetition time (TR) = 2000 ms, echo time (TE) = 2.23 ms, flip angle = 8°, field of view (FOV) = 240 × 240 × 240, voxel size = 0.9 × 0.9 × 0.9 mm. fMRI scan: acquisition time = 488 s, matrix = 64 × 64 × 36 slices, TR = 2000 ms, TE = 30 ms, dynamic scans = 240, flip angle = 90°, FOV = 224 mm × 224 mm × 224 mm, voxel size = 3.5 mm × 3.5 mm × 4.0 mm. DWI: acquisition time = 945 s, matrix = 112 × 112 × 46 slices, TR = 6,600 ms, TE = 107 ms, FOV = 224 mm × 224 mm × 224 mm, voxel size = 2.0 mm × 2.0 mm × 3.0 mm. A multi-shell protocol was used with b-values of 0, 1,000, and 2000.

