### Statistical analysis

2.9

All data from enrolled participants will be collected and analyzed. Descriptive statistics will be used to summarize baseline characteristics. The Shapiro–Wilk test will be applied to assess the normality of continuous variables. For normally distributed quantitative data, results will be presented as mean ± standard deviation (SD). For non-normally distributed data, results will be presented as median and interquartile range (IQR). Categorical variables will be expressed as frequencies and percentages, and between-group comparisons will be made using the chi-square test or Fisher’s exact test, as appropriate. To assess the treatment effects over time, linear mixed-effects models will be used to analyze repeated measures, accounting for both fixed effects (group, time, group × time interaction) and random effects. Both intention-to-treat (ITT) and per-protocol (PP) analyses will be conducted. For the ITT analysis, missing data will be handled using the Last Observation Carried Forward (LOCF) method, as previously used in acupuncture studies (40, 41). The PP analysis will include participants who complete the intervention and outcome assessments without major protocol deviations. Statistical significance will be defined as a two-sided *p*-value <0.05. All statistical analyses will be performed using SPSS version 24.0.

Lifestyle adherence scores will be summarized during the 16-week intervention period. The mean weekly adherence score will be calculated for each participant based on the Healthy Lifestyle Adherence Scoring System. Between-group differences in lifestyle adherence will be evaluated descriptively. Where appropriate, the mean lifestyle adherence score will be included as a covariate in adjusted analyses for clinical outcomes and rs-fMRI-related exploratory analyses. Sensitivity analyses may also be conducted to examine whether the main findings remain robust after accounting for lifestyle adherence or excluding participants with marked lifestyle non-compliance.

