fMRI data will be processed using MATLAB R2017b in conjunction with the CONN functional connectivity toolbox (version 20). Standard preprocessing procedures will include slice timing correction, realignment, spatial normalization to MNI space, smoothing, artifact detection, linear trend and covarients removal, and temporal band-pass filtering. Hypothalamus and other relevant brain regions will be defined as the primary region of interest (ROI) for functional connectivity analysis.

To explore the association between central functional connectivity changes and peripheral ovarian reserve-related biomarkers, an exploratory correlation analysis will be performed. For participants with available imaging and peripheral biomarker data at both baseline and week 16, changes in hypothalamus-centered functional connectivity values will be calculated and correlated with changes in AFC, FSH, and LH from baseline to week 16. Pearson correlation analysis will be used when the variables are normally distributed, whereas Spearman rank correlation analysis will be applied for non-normally distributed variables. When multiple functional connectivity clusters or multiple peripheral biomarkers are examined, appropriate multiple-comparison correction will be applied to adjust for multiple comparisons. These analyses will be considered exploratory and hypothesis-generating, and will not be interpreted as evidence of causal brain-ovary regulation.

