## Discussion

3

With the societal trend toward delayed marriage and childbirth, female fertility is declining with advancing age. Coupled with unhealthy lifestyle habits and excessive work-related stress, the incidence of DOR has been rising steadily and is now increasingly observed in younger women.

This protocol evaluates the potential effects of YYRM in patients with DOR using a multidimensional assessment framework. AFC, AMH, FSH, and LH provide complementary information on ovarian reserve status from morphological, biochemical, and endocrine perspectives. AFC reflects the recruitable follicle pool, AMH provides relatively stable biochemical information on ovarian reserve, and FSH and LH are more closely related to HPO-axis feedback regulation (42). Therefore, these indicators together may help characterize ovarian reserve changes after YYRM more comprehensively than any single marker alone. The rs-fMRI component of this study is exploratory and is intended to investigate potential central regulatory pathways in patients with DOR, rather than to serve as the primary endpoint or to establish confirmatory evidence of brain-ovary causality.

According to the TCM theory, DOR is fundamentally associated with kidney yang deficiency, which reflects a functional insufficiency in sustaining reproductive vitality rather than a localized ovarian disorder (43). Based on this pathogenesis, YYRM was designed according to the therapeutic principle of warming yang and tonifying the kidney. Therefore, the selection of acupoints in this protocol emphasizes points traditionally associated with supporting kidney yang and reproductive function.

In this study, Shenque (CV8) and Mingmen (GV4) were selected as primary acupoints for intervention. CV8, located in the center of the umbilicus and associated with the Conception Vessel. It is traditionally regarded as a key site for supporting vital essence and reproductive function (44). GV4, an acupoint of the governor vessel, is located at the lumbar spine. Stimulating GV4 can tonify and nourish the Kidney Yang. Stimulation at these sites may engage somatosensory and autonomic afferent pathways that influence hypothalamus-centered neural activity (45, 46). Through this pathway, moxibustion may modulate central neuroendocrine regulation related to ovarian function.

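### The brain–ovary correlation has no term for randomised arm, so arm differences alone can produce it; separately, AMH is missing from the biomarker list without a reason

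*Protocol article*

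**What the plan says.** The Statistical analysis section (2.9) of the protocol article sets out one analysis linking imaging to ovarian markers.

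- **Who:** "For participants with available imaging and peripheral biomarker data at both baseline and week 16". Arm is not mentioned. The Rs-fMRI section (2.7.4) has every participant scanned at weeks 0 and 16, so both arms contribute.
- **What:** "changes in hypothalamus-centered functional connectivity values will be calculated and correlated with changes in AFC, FSH, and LH from baseline to week 16".
- **Test:** "Pearson correlation analysis will be used when the variables are normally distributed", and Spearman otherwise. No partial correlation, group term or within-arm analysis is mentioned.
- **Covariates:** where appropriate, "the mean lifestyle adherence score will be included as a covariate in adjusted analyses for clinical outcomes and rs-fMRI-related exploratory analyses". No other covariate is named for the imaging analyses.
- **Multiplicity:** "appropriate multiple-comparison correction will be applied to adjust for multiple comparisons", with no method named.
- **Status:** exploratory and hypothesis-generating, with a causal reading expressly ruled out.

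On AMH, the Secondary outcomes section (2.7.2) draws blood at weeks 0, 16 and 32 "to measure AMH, FSH, and LH levels". The Introduction treats AMH, alongside AFC, as an established marker of reserve, and the Discussion says that "AMH provides relatively stable biochemical information on ovarian reserve". AMH is nevertheless absent from the correlation list.

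**The concern.** The trial is built on the idea that moxibustion changes both ovarian reserve and hypothalamic connectivity. If it does, arm is a common cause of the two change scores. A correlation across all participants then combines two things: whether women with larger brain changes also have larger ovarian changes, and whether the two arms differ on average in both. Only the first is evidence of a brain–ovary link beyond the treatment comparison itself. An unadjusted correlation cannot tell them apart.

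The open-label design adds to this. The Discussion concedes that specific and non-specific effects of active treatment cannot be fully separated, and either kind would act on the correlation in the same way.

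At stake is the reading of the only planned analysis that joins the imaging to the ovarian outcomes. The Discussion also hopes to find imaging markers of treatment response, and a correlation produced by arm means would not support one.

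The AMH point is distinct. The stated purpose is to relate connectivity to markers of ovarian reserve, yet one of the two established markers is left out while FSH and LH are kept. That is an unexplained gap in the list and has no bearing on the spurious correlation.

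**Working it through.** The plan gives no N, power or expected correlation for this analysis, so there is no stated figure to reproduce.

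**Inputs**
- Evaluable sample: 56, 28 per arm (Sample size estimation, 2.8).
- AFC effect: 2.8 quotes 4.16 ± 0.86 and 3.00 ± 1.69. The difference is 4.16 − 3.00 = 1.16. The pooled SD is √((0.86² + 1.69²)/2) = 1.34. The effect is 1.16/1.34 ≈ 0.87 SD.
- Connectivity effect: not given. Assumed range 0 to 1.0 SD.
- Within-arm correlation: set to zero, so any pooled correlation is an artefact.

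**Expected pooled correlation.** With 1:1 arms, unit within-arm variances and standardised arm differences d₁ and d₂, the pooled covariance is d₁d₂/4 and each pooled variance is 1 + d²/4. Hence

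r = (d₁d₂/4) / √[(1 + d₁²/4)(1 + d₂²/4)].

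For d₁ = 0.865 and d₂ = 0.5: the numerator is 0.108, the denominator is √(1.187 × 1.0625) = 1.123, and r = 0.096.

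**Rejection rates.** 20,000 simulated trials per row, 28 + 28, normal data, Pearson, two-sided 0.05, before any multiplicity correction. The adjusted test removes arm means and uses N − 3 = 53 degrees of freedom.

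| Connectivity effect (SD) | Expected pooled r | Unadjusted | Adjusted for group |
|---|---|---|---|
| 0 | 0.00 | 5% | 5% |
| 0.3 | 0.06 | 7% | 5% |
| 0.5 | 0.10 | 11% | 5% |
| 0.8 | 0.15 | 19% | 5% |
| 1.0 | 0.18 | 26% | 5% |

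The critical |r| at N = 56 is 2.005/√(54 + 2.005²) = 0.263, above every expected r in the table.

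**Sensitivity to the AFC effect.** Section 2.8 also states a difference of 1.8. With the same SD that is 1.8/1.34 = 1.34 SD, and the unadjusted rates become 5%, 10%, 17%, 34% and 48%.

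**Sensitivity to multiplicity.** No method is named. Assuming Bonferroni over the three listed biomarkers, the per-test level is 0.05/3 = 1.7%. With the AFC effect at 0.87 SD, the unadjusted test then rejects in about 4 to 5% of trials at a connectivity effect of 0.5 SD, and in about 11% when the connectivity effect is also 0.87 SD. The rates fall, but remain several times nominal.

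**The case against.** **Pooling is not stated.** The text is silent about arm, within-arm correlations would be compatible with it, and an article may leave such detail to a fuller document. It is right that pooling is an inference. But the article does specify the set, the variables and the test, and followed literally they give one correlation across everyone. The lifestyle covariate shows that some adjustment is foreseen, but it does not stand in for arm.

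**The analysis is labelled exploratory and non-causal, and a correction is planned.** Both are real safeguards and they lower the priority. The label limits what may be concluded, and the correction limits chance findings. Neither takes the arm difference out of the estimate.

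**The between-arm part could be genuine.** If connectivity truly carried the treatment effect, some of the pooled correlation would be real. The unadjusted analysis cannot show this, however, because the same value arises with no within-arm link at all.

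**AMH may have been left out on purpose.** The Discussion ties FSH and LH more closely to feedback in the hypothalamic–pituitary–ovarian axis, which could justify pairing them with a hypothalamic seed. That is plausible, but it is not given as the reason, and AFC is kept although that reason does not cover it.

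**A stronger reading to avoid.** A reader might infer that a positive trial will tend to bring a positive correlation with it. The figures do not support that. Even at a connectivity effect of 1.0 SD with the AFC effect at 0.87 SD, 74% of trials show no significant correlation. If treatment does not move connectivity, there is no inflation however well AFC responds.

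**Conclusion.** The point holds in a conditional form. As written, the correlation is open to confounding by randomised arm. With no true within-arm association, its false-positive rate runs from 5% to 26% as the connectivity effect goes from 0 to 1.0 SD, where group adjustment keeps it at about 5%. This rests on the plain reading that arms are pooled, on 56 evaluable participants, on an AFC effect of about 0.87 SD, and on an assumed connectivity effect for which the documents give no value. The rates apply to AFC; no effect sizes are given for FSH or LH.

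The missing AMH is a separate, minor inconsistency within the article and contributes nothing to the artefact.

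No confirmatory conclusion depends on this analysis, so the priority is low to moderate.

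**What to change.** Replace the bivariate tests with partial correlations (Pearson or Spearman) adjusted for randomised group, or with a regression of biomarker change on connectivity change plus group. Report the within-arm correlations beside them, so that a reader can see whether the association is present and similar in each arm. If within-arm analysis was already intended, one sentence saying so settles the point.

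Add AMH change to the biomarker list and to the multiplicity correction, or state why it is left out.

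The cost is one degree of freedom for the group term and one more biomarker in the correction. AMH is already collected at the same visits, so no new data are needed and only the analysis wording changes.

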## Discussion

3

With the societal trend toward delayed marriage and childbirth, female fertility is declining with advancing age. Coupled with unhealthy lifestyle habits and excessive work-related stress, the incidence of DOR has been rising steadily and is now increasingly observed in younger women.

This protocol evaluates the potential effects of YYRM in patients with DOR using a multidimensional assessment framework. AFC, AMH, FSH, and LH provide complementary information on ovarian reserve status from morphological, biochemical, and endocrine perspectives. AFC reflects the recruitable follicle pool, AMH provides relatively stable biochemical information on ovarian reserve, and FSH and LH are more closely related to HPO-axis feedback regulation (42). Therefore, these indicators together may help characterize ovarian reserve changes after YYRM more comprehensively than any single marker alone. The rs-fMRI component of this study is exploratory and is intended to investigate potential central regulatory pathways in patients with DOR, rather than to serve as the primary endpoint or to establish confirmatory evidence of brain-ovary causality.

According to the TCM theory, DOR is fundamentally associated with kidney yang deficiency, which reflects a functional insufficiency in sustaining reproductive vitality rather than a localized ovarian disorder (43). Based on this pathogenesis, YYRM was designed according to the therapeutic principle of warming yang and tonifying the kidney. Therefore, the selection of acupoints in this protocol emphasizes points traditionally associated with supporting kidney yang and reproductive function.

In this study, Shenque (CV8) and Mingmen (GV4) were selected as primary acupoints for intervention. CV8, located in the center of the umbilicus and associated with the Conception Vessel. It is traditionally regarded as a key site for supporting vital essence and reproductive function (44). GV4, an acupoint of the governor vessel, is located at the lumbar spine. Stimulating GV4 can tonify and nourish the Kidney Yang. Stimulation at these sites may engage somatosensory and autonomic afferent pathways that influence hypothalamus-centered neural activity (45, 46). Through this pathway, moxibustion may modulate central neuroendocrine regulation related to ovarian function.

The hypothalamus was selected as the primary seed region because it is a key central node in reproductive neuroendocrine regulation and plays a direct role in gonadotropin-releasing hormone signaling within the HPO axis (47). For a hypothesis-driven seed-based rs-fMRI design, the hypothalamus provides a biologically plausible entry point for exploring the potential central mechanisms linking moxibustion and ovarian function. This choice is also consistent with a DOR neuroimaging study protocol that adopted a hypothalamus-centered framework (15).

The primary objective of this study was to assess the clinical efficacy of moxibustion in women with DOR and to investigate its potential central mechanisms using fMRI. By incorporating fMRI as a complementary neuroimaging technique, we aimed to explore the central regulatory pathways associated with ovarian function and provide novel insights into the neuroendocrine basis of DOR rather than to establish causal mechanisms. Our findings are expected to enhance understanding of the therapeutic potential of moxibustion in improving ovarian reserve and to identify objective, neuroimaging-based markers for evaluating treatment response. Such evidence may further support the standardization of moxibustion assessment protocols in clinical trials and promote its broader clinical application in reproductive medicine.

This study innovatively integrates fMRI to investigate the impact of moxibustion on brain activity patterns. However, there are still several limitations in this trial: First, this study adopts an open-label design and does not include a sham moxibustion or placebo control. Due to the thermal and sensory characteristics of moxibustion, double-blinding of both participants and practitioners was not feasible, which may introduce expectancy bias. Therefore, the present study cannot fully separate the specific effects of YYRM from nonspecific effects associated with receiving active treatment. Second, our study is a single-center trial conducted solely in one hospital in China. thus, the findings require validation in larger, more diverse populations. Third, the sample size was relatively small, and this was a single-center, open-label study. These factors may limit the strength of the evidence generated by the present study. Therefore, the findings of this trial should be regarded as preliminary and interpreted with caution. Fourth, while the hypothalamus serves as a focused entry point for exploring ovarian-related central regulation, studies have also shown that other regions and networks may play a role in the central neuroendocrine regulation (48–50). We will consider investigating these regions in future studies, if necessary, to further elucidate the underlying mechanisms.
